**Figure 4 figure4:**
[figure not shown]
Number of partners and age groups selection box.

A trained nurse/counselor will proceed to perform two rapid HIV tests and communicate the results to the participant. If the results are HIV positive, the participant will be counseled and encouraged to commence antiretroviral therapy at a clinic of their choice. If the results are HIV negative, the participant will be eligible for visit 2 (3 months after visit 1) and will be issued with an appointment card. If the results are discordant, the nurse/counselor will be required to repeat testing. Additionally, the participant will be sent visit 2 appointment reminders through text messages monthly.

#### Confirmatory Procedures

HIV status will be confirmed using the rapid diagnostic kits in-use (First Response HIV 1-2-0 and Alere DetermineHIV-1/2) at the testing site. If the confirmatory rapid test is HIV positive, the participant will be referred to a clinic of their choice for treatment and care.

In the event the second rapid test shows a negative result, the HIV status will be considered indeterminate, and all tests will be repeated (Textbox 1) [13].

Interpreting test results. RDT: rapid diagnosis test.RDT1 (positive) + RDT2 (positive) = positiveRDT1 (negative) + RDT2 (negative) = negativeRDT1 (negative) + RDT2 (positive) = indeterminate (repeat test)RDT1 (positive) + RDT2 (negative) = indeterminate (repeat test)

### Data Analysis

The study endpoints for this trial are concerned with the proportion for concordance of the participants’ risk assessment score with the confirmatory test results.

An interim analysis of the results will be reviewed after visit 1 has been completed. All the recorded risk behavioral scores will be analyzed for any correlation between HIV testing outcomes.

In addition, the analysis plan will include an evaluation performed at visit 2, identifying cases where an initial nonreactive test (at visit 1) has resulted in a change to a reactive test result (at visit 2).

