A risk assessment tool is a set of simple and easy*-*to*-*understand questions *that* are answered by the participant(s)*,* and based on the responses, a risk probability is calculated. The questions are related to demographics, sexual behavior, sexual history, personal behavior, lifestyle*,* and medical history. The questions are scientifically designed based on the HIV correlation data from published research and clinical trials. The tool makes use of scientific algorithms to determine the risk probability and *provides* the outcome as low risk*,* medium risk*,* or high risk. Diagnostic assistive assessment is performed on a mobile device by the patients themselves*,* thus eliminating external influences and hence providing more accurate information.

In 2019-2020, a feasibility study was conducted with over 1000 participants at the Wits Reproductive Health and HIV Institute’s (WRHI) HIV self-testing assessment and research (HSTAR) Africa site in Johannesburg, South Africa. This study sought to understand the correlation between HIV status and factors such as demographics, sexual behavior and history, personal behavior and lifestyle, and symptoms, individually.

Analysis of the data collected from this feasibility study showed correlations between HIV status and all the variables. The main inference made was that patients can be grouped based on multiple factors as follows:

Primary features (demographics)Secondary features (lifestyle)Tertiary features (sexual behavior)Auxiliary features (symptoms)

Examples of the detailed analysis are shown in Figure 1.

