## Methods

### Objectives

The primary objective of this study is to assess the participants’ risk behavior using an automatic machine-guided tool and compare these results to HIV outcomes. The secondary objectives are:

To evaluate the participants’ interaction with the tool in terms of effectiveness and efficiency, that is, successful/unsuccessful completion and difficulty using the toolTo assess the ability of the participants to correctly comprehend and complete specific behavioral questions on a digital platformTo understand user experience and satisfaction with the overall process and recommend improvements for machine-guided tool development

The study is registered on the South African National Clinical Trial Registry (www.sanctr.gov.za; DOH-27-042021-679) and was approved by the University of Witwatersrand Human Research Ethics Committee (HREC; ethics reference no. 200312) on August 20, 2020.

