### Sample Size

A purposive sample of 600 participants across all sites (200 per site) will be recruited for this study. In machine learning, the required sample size for a study has not developed into a clear-cut methodology and requires data to compare model performance to relative data size. Therefore, the initial feasibility study maximized on available funding to determine an initial sample size for method validation and to allow for the ability to use the initial sample to compare the performance of the model to the sample size. As seen in Figueroa et al [12], 80-560 samples were required to reach a root-mean-square error below 0.01. A sample size of 600 based on the observations of Figueroa et al [12] will facilitate comparison between model sample size and model performance in order to inform further investigations and machine learning model development. As the device is intended to be used by both males and females from the general population, this assessment aims to recruit as close to a 50% breakdown per gender as possible.

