#### Machine Learning Algorithm

The first phase of this machine-guided diagnostic study will be used to compare potential supervised learning algorithms to determine which algorithm is the most robust in variable variation. The algorithms that will be compared are K-nearest neighbor, logistic regression, neural network, random forest, support vector machine, and XGBoost. These models will be compared using a confusion matrix by comparing sensitivity, specificity, accuracy, precision, and negative predictive value. When comparing models, the relative risk of a false negative versus a false positive will be taken into consideration to minimize the risk of potentially high-risk patients not being flagged for further screening.

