#### Error and Failure Rates

Critical errors occur when participants make operational errors during interaction with the machine-guided tool. Project staff will aid participants, if needed, to ensure accurate completion of all behavioral questions that contribute directly to risk assessment scores.

The failure rate (cases where the risk score is high and the test result remains negative for both visits) will be identified and reported as the number or a percentage of failed cases of the total number of cases completed in the study.

It should be noted that failure due to critical errors (participants not being able to successfully complete the digital assessment) will not be included in the analysis.

The type of behavioral questions and the weighted score for each will be monitored and evaluated for continuous improvement and refinement purposes.

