#### Skewed Data

The participants enrolled in this study who are either HIV negative or of unknown HIV status will cause a lower HIV prevalence in the sample data set. However, this will be done so as to remove the possibility of participants who are HIV positive creating a bias in the supervised learning, as these people may have altered behavior due to being HIV positive, which may result in risk reduction behavior, reducing the sensitivity and accuracy of the model. The skewed data set will be accounted for in the second phase of the study, where participants will perform two visits, including a follow-up HIV test, which will allow for the analysis of a comparison to the predictive ability of the machine learning model created in phase 1.

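### The stated endpoint, raw concordance with the HIV test, is dominated by true negatives in this sample and can rank a tool that flags nobody above a useful one

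*Protocol article*

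**What the plan says.** The primary objective (Objectives) is "to assess the participants’ risk behavior using an automatic machine-guided tool and compare these results to HIV outcomes". The Data Analysis section turns this into an endpoint: "The study endpoints for this trial are concerned with the proportion for concordance of the" score with the confirmatory test result. No target value is given.

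The two things compared are on different scales. The Introduction says that the tool reports "the outcome as low risk*,* medium risk*,* or high risk". Under Confirmatory Procedures the reference is positive or negative, and indeterminate results are repeated.

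On the sample, "A purposive sample of 600 participants across all sites (200 per site) will be recruited" (Sample Size). Known HIV-positive people are excluded (Exclusion Criteria). The Skewed Data section accepts that the eligibility rules "will cause a lower HIV prevalence in the sample data set", without a figure.

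Other performance measures appear in three places:

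- Machine Learning Algorithm: candidate algorithms are judged by "comparing sensitivity, specificity, accuracy, precision, and negative predictive value", and "the relative risk of a false negative versus a false positive will be taken into consideration".
- Sensitivity Analysis: despite its heading, this describes model performance in the validation set, with sensitivity, specificity and accuracy from a confusion matrix.
- Error and Failure Rates: a failure rate is reported, where failures are "cases where the risk score is high and the test result remains negative for both visits".

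**The concern.** The proportion of scores that agree with the test is overall accuracy. When few participants are positive, accuracy is mostly specificity, and missing every positive costs little. The Machine Learning Algorithm section says that the aim is to avoid leaving high-risk people unflagged, yet the endpoint gives that error almost no weight. The failure rate gives it none.

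The second difficulty is that agreement between a three-level score and a two-level test is undefined until each level, medium included, is assigned to a test result. If that assignment is made after the data are seen, the endpoint can move a long way.

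At stake is the main conclusion. A high concordance figure could be read as evidence that the tool works when it detects few cases or none.

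**Working it through.** The article states no concordance target, prevalence or power, so there is no figure of its own to reproduce.

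**Inputs.** N = 600 (Sample Size). Prevalence p is not given, so 3%, 5%, 10% and 20% are assumed. Sensitivity (Se) and specificity (Sp) of the example tools are also assumed.

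**Formula.** Concordance = p × Se + (1 − p) × Sp. For a tool that calls everyone low, Se = 0 and Sp = 1, so concordance = 1 − p.

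**Counts at p = 5%.** There are 600 × 0.05 = 30 positives and 570 negatives.

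- All-low tool: 570/600 = 95% concordant, 0 of 30 positives found.
- 80%/80% tool: 0.8 × 30 = 24 positives found and 0.8 × 570 = 456 negatives correct, so (24 + 456)/600 = 80% concordant.

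**Break-even.** A tool beats all-low when p × Se > (1 − p) × (1 − Sp). True positives must then outnumber false positives, so more than half of those flagged must be positive. At Se = 80% this requires Sp > 1 − 0.8p/(1 − p).

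| Prevalence (assumed) | All-low | Se 80%, Sp 80% | Se 90%, Sp 90% | Se 90%, Sp 95% | Sp needed at Se 80% |
|---|---|---|---|---|---|
| 3% | 97% | 80% | 90% | 94.85% | 97.5% |
| 5% | 95% | 80% | 90% | 94.75% | 95.8% |
| 10% | 90% | 80% | 90% | 94.5% | 91.1% |
| 20% | 80% | 80% | 90% | 94.0% | 80.0% |

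At 3% and 5% the all-low tool outscores all three example tools. At 10% it ties with 90%/90% and loses to 90%/95%. At 20% it ties with 80%/80% and loses to the other two.

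**Failure rate.** An all-low tool has no high scores, so its failure rate is 0. For the 80%/80% tool at 5%, take flagged to mean high and suppose that everyone completes both visits with unchanged results. Its failures are 0.2 × 570 = 114, or 114/600 = 19%. Its 6 missed positives are not counted, nor are the 30 that all-low misses.

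**Three-level score.** As an illustration only, assume low/medium/high shares of 60/25/15% in negatives and 15/30/55% in positives, with p = 5%.

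- Medium counted as low: 0.05 × 0.55 + 0.95 × 0.85 = 83.5%.
- Medium counted as high: 0.05 × 0.85 + 0.95 × 0.60 = 61.25%.
- Medium always discordant: 0.05 × 0.55 + 0.95 × 0.60 = 59.75%.
- Medium excluded: medium makes up 0.05 × 0.30 + 0.95 × 0.25 = 25.25%, so 59.75/74.75 = 79.9%.

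The same data give about 60% to 84%, depending on a rule that the article does not state.

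**The case against.** The strongest reply is that the plan does not rely on concordance alone. The Abstract describes output metrics that treat scores as predictions and tests as truth. The Machine Learning Algorithm and Sensitivity Analysis sections then list sensitivity, specificity and more, with attention to false negatives. A tool that found no case would show 0% sensitivity in that output. This stands, and it limits the harm. A reader might infer that the study would be blind to a useless tool, and the document does not support that. But these measures are assigned to choosing an algorithm and describing validation-set performance. They are not named as the endpoint, and they need the same unstated cut.

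A reader might also infer that concordance is highest for an all-low tool, or that any useful tool would look worse. Neither is so. A perfect tool scores 100%, and the table shows good tools matching or beating all-low at 10% to 20% prevalence. The size of the problem depends on a prevalence that the article does not give.

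Third, this is a condensed article, and the full protocol or analysis plan may say how medium is handled. That is fair, so the missing mapping alone would be a weak point. The choice of endpoint is different, because it is stated, and a mapping rule would not cure its dependence on prevalence.

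Finally, the Skewed Data section says that the second phase will account for the skew. But only people who test negative at visit 1 go on to visit 2, so follow-up does not restore the balance.

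**Conclusion.** The concern holds in a limited form. As stated, the endpoint can place a tool with zero sensitivity above one that finds most cases, and the failure rate leans the same way. At an assumed 5% prevalence the gap is 95% against 80% in favour of the tool that finds nobody. At 20% the two tie. The direction follows from arithmetic and from the article's own statement that prevalence will be reduced. The size rests on the assumed prevalence and tool performance. The planned confusion-matrix metrics reduce the risk of a misleading report but do not correct the endpoint, and on the text shown its value is not fixed for a medium score.

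**What to change.** 1. In Data Analysis, replace concordance as the endpoint with sensitivity and specificity against the resolved HIV result, each with a 95% confidence interval.
2. Prespecify one grouping of low, medium and high into two classes, and use it consistently in Error and Failure Rates, where only high is mentioned now.
3. In Error and Failure Rates, count a low score with a positive test as a failure alongside a high score with negative tests. Report the two separately. Their sum under a two-class score is 1 minus concordance and would again favour all-low (30/600 = 5% against (114 + 6)/600 = 20% in the example above).
4. Keep concordance as a descriptive figure, always beside 1 minus prevalence.

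The change is one of wording and uses data already to be collected. The cost is that the headline figure may look less favourable. The sensitivity interval will also rest on few people (30 at 5% prevalence, fewer in a validation subset), which raw concordance would have hidden.

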#### Machine Learning Algorithm

The first phase of this machine-guided diagnostic study will be used to compare potential supervised learning algorithms to determine which algorithm is the most robust in variable variation. The algorithms that will be compared are K-nearest neighbor, logistic regression, neural network, random forest, support vector machine, and XGBoost. These models will be compared using a confusion matrix by comparing sensitivity, specificity, accuracy, precision, and negative predictive value. When comparing models, the relative risk of a false negative versus a false positive will be taken into consideration to minimize the risk of potentially high-risk patients not being flagged for further screening.

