### Blinding of Results

This will be a blinded study. Participants will not be aware of their risk assessment scores. There will be no randomization of participants, as all participants will be required to interact with the machine-guided tool. This study will make use of supervised learning in which the data set will be collected and then used to train and test the machine learning model that has been created. The data will be collected in a specific area, and selection will be random. The data, however, will be split into training and validation data using a randomized split algorithm commonly found in statistical and data processing languages such as R and Python.

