#### Sensitivity Analysis

The performance of the model will be analyzed using the validation data set from the data split using a confusion matrix (Figure 5) that will allow for the calculation of sensitivity, specificity, and accuracy.

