#### Post Hoc Analysis

In machine learning, post hoc analysis is not commonly performed, and a comparison of model performance through the analysis of a confusion matrix and confidence curves offers an alternative to conventional omnibus tests [15].

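### Phase 1 is to find the algorithm most robust to variable variation, but the stated comparison does not measure robustness

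*Protocol article*

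**What the plan says.** Under Machine Learning Algorithm, the protocol article gives phase 1 the task to "determine which algorithm is the most robust in variable variation". The candidates are "K-nearest neighbor, logistic regression, neural network, random forest, support vector machine, and XGBoost". The method follows directly: "These models will be compared using a confusion matrix by comparing sensitivity, specificity, accuracy, precision, and negative predictive value". In choosing, "the relative risk of a false negative versus a false positive will be taken into consideration"; no weight or threshold is attached.

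Two other sections say where the matrix comes from. Under Blinding of Results, the data are "split into training and validation data using a randomized split algorithm". Under Sensitivity Analysis, performance is "analyzed using the validation data set from the data split using a confusion matrix".

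Under Post Hoc Analysis the article states that "a comparison of model performance through the analysis of a confusion matrix and confidence curves offers an alternative to conventional omnibus tests". It does not describe how the curves are built or what result would count as a difference.

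The Skewed Data section then takes the model created in phase 1 into the second phase, where its predictions are compared with follow-up HIV tests.

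**The concern.** The article states both an aim and a method for phase 1, and the method does not answer the aim. Robustness to variable variation concerns change: how far performance moves when inputs are altered or dropped, or when the people or sites differ. The five listed metrics are levels of performance under one set of conditions.

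The choice made in phase 1 determines which model phase 2 evaluates. If it is reported as the most robust algorithm, readers will take that as evidence that it should hold up in other settings. That matters here because the Design section names the move from a clinic to field sites as the main change from the feasibility study. The planned comparison would not supply that evidence.

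A second, smaller concern is that nothing stated tells the analyst when an observed difference between algorithms is larger than chance would give. With few HIV-positive participants in a validation set, chance differences in sensitivity can be large.

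**Working it through.** **1. Does the method measure the aim?**

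| Element | What the article gives |
|---|---|
| Aim | robustness in variable variation |
| Metrics | five, all from a confusion matrix |
| Data | validation part of a randomized split |
| Definition of robustness | none stated |
| Altering or omitting variables, repeating the split, comparing algorithms by site | none stated |

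A simple case shows the gap. Take three sites with equal numbers of positives. Algorithm A has sensitivity *s* at every site. Algorithm B has *s + d*, *s* and *s − d*. B's pooled sensitivity is (*s + d + s + s − d*)/3 = *s*, the same as A's. The two have identical pooled sensitivity, although A is stable and B is not. The same argument applies to the other metrics and to variation in the input variables.

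**2. How large could chance differences be? (illustration only)**

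The article's one design figure reproduces: 3 sites × 200 = 600. It gives no precision target, prevalence or split ratio, so the following are assumptions.

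- Validation share 20–30% and HIV prevalence 5–10%.
- Positives in the validation set: 600 × 0.20 × 0.05 = 6; 600 × 0.30 × 0.05 = 9; 600 × 0.20 × 0.10 = 12; 600 × 0.30 × 0.10 = 18.
- All six algorithms have true sensitivity 75%. No other value was tried.
- Algorithm *j* detects positive participant *i* when √ρ·c_i + √(1−ρ)·e_ij < Φ⁻¹(0.75), with c and e independent standard normal and ρ from 0.3 to 0.8.
- Gap = highest minus lowest observed sensitivity among the six, averaged over 20,000 simulated validation sets.

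| Positives | Mean gap, ρ = 0.8 to 0.3 (points) | Sets with a single top algorithm on sensitivity |
|---|---|---|
| 6 | 25 to 38 | about 30 to 42% |
| 12 | 20 to 28 | about 47 to 58% |
| 18 | 16 to 23 | about 55 to 66% |

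Part of this is granularity: at 6 positives one participant is 1/6 = 16.7 points. Under wider assumptions (prevalence 2–10%, validation share 20–50%, ρ from 0 to 0.8) the mean gap runs from 13 points at 30 positives to 64 points at 2. For one algorithm that detects 7 of 9 positives, the exact 95% interval for sensitivity is about 40% to 97%.

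**3. Does this carry over to a comparison on several metrics?**

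Only in part. Suppose one algorithm is truly better, at 80% against 70% for the other five. Choosing on sensitivity alone, with ties broken at random, finds it in 31–36% of sets at 6 positives, about 39–49% at 12 and about 46–59% at 18 (chance is 1/6 = 17%). If the same advantage also holds for specificity and the choice is made on sensitivity plus specificity, it is found in from a little over half to 72% of sets at 6 positives, about 67–84% at 12 and about 78–92% at 18. Noise falls, but even this says nothing about robustness.

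**The case against.** Several stronger readings are tempting, and the article does not support them.

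- **That the plan relies on bare confusion matrices in place of a test.** It names confidence curves as well, and these may convey uncertainty. Choosing a model without a significance test is not in itself an error.
- **That a winner is always named, even among equal algorithms.** No sentence says the highest point estimate wins or forbids reporting a tie. In the illustration a single top algorithm on sensitivity appears in only about 30–66% of sets.
- **That sensitivity is weighed most, so the choice is mostly noise.** The article lists five metrics and says that false negatives and false positives will be weighed against each other. It does not rank sensitivity first, and step 3 shows that using more than one metric improves the choice considerably.

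It is also fair to say that the data for phase 1 are unclear. The Skewed Data section describes the second phase as the one with two visits, and the Design section builds on a feasibility study of over 1000 participants, so the 6 to 18 positives may not be the right base. The Sample Size section plans to relate performance to sample size, which covers one kind of variation, though not variation in variables. Repeated splits and handling of ties are details that a condensed article may leave to a fuller document.

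What remains is the mismatch. The article itself pairs a robustness aim with metrics that cannot show robustness. That is a statement to correct, not a detail left for elsewhere.

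**Conclusion.** The point holds as a mismatch between aim and method. Followed as written, phase 1 could report which algorithm classified best in the validation data, but not which is most robust to variable variation. This conclusion rests on the article's wording alone and needs no numerical assumption.

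The figure of about 16 to 38 points for the gap among equal algorithms is secondary. It rests on the assumed prevalence, split, correlation and common true sensitivity of 75%, and applies to sensitivity taken alone. It shows that sensitivity by itself would separate six algorithms poorly, so a stated way to judge differences is worth having. It does not show that the planned comparison on several metrics would fail.

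**What to change.** In the Machine Learning Algorithm section, do one of two things.

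1. **Keep the robustness aim and measure it.** Compare the six algorithms on the same participants by repeated stratified resampling within the training data. Report paired differences with intervals that allow for the overlap between resamples, since naive intervals would be too narrow. Define robustness as the spread of performance across resamples, across sites, and across runs in which variables are left out. Allow the report to say that algorithms were not distinguishable. Six algorithms give 6 × 5/2 = 15 pairs, and 15 unadjusted comparisons at 5% would carry a familywise error of 1 − 0.95¹⁵ = 0.54 if independent. The intervals should therefore be adjusted or presented as descriptive.
2. **Drop the robustness wording.** Claim only the best observed classification performance in the validation data.

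In either case, state which data phase 1 uses and add a sentence on how the confidence curves will be read. The Post Hoc Analysis statement need not be deleted, and no default algorithm need be imposed.

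The cost is computing time and rewording, with no new data. The downside of the first option is that no algorithm may emerge as clearly best.
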